### Recruitment process

The trial is expected to take up to 30 months to complete recruitment. Participants will be recruited from the Charité Universitätsmedizin Berlin. Following verbal and written study information in form of the patient information sheet and extensive discussion with a clinical trial physician, patients will get at least 24 h time to consider participation.

Patients who meet all the inclusion criteria and none of the exclusion criteria listed in Table 1 will be invited to provide written informed consent.

**Table 1 Tab1:** Nikolo trial inclusion and exclusion criteria

**Inclusion criteria**
Disease related
Patients with metachronous or synchronous metastases of a colorectal cancer progressing under standard therapy
No proven brain metastases
No curative option available
No standard therapy available
At least one metastasis has to be measurable according to RECIST V 1.1 in X-ray computed tomography or magnetic resonance imaging (not older than 2 weeks before inclusion into the trial)
Demographic
Age > 18 years
Eastern Cooperative Oncology Group performance status ECOG 0–1
Laboratory
Absolute neutrophil count ≥ 1.5 × 10^9^/ L
Platelet count ≥ 100 × 10^9^/L
Leukocytes ≥ 1.0 × 10^9^/L
Hemoglobin ≥ 9.0 g/dL or 5.59 mmol/l
Bilirubin ≤ 2 x Upper Limit of Normal (ULN) if not due to Gilbert’s syndrome
AST ≤ 2.5xULN in patients without liver metastases or ≤ 5.0xULN in patients with liver metastases
ALT ≤ 2.5xULN in patients without liver metastases or < 5.0xULN in patients with liver metastases
Adequate renal function (creatinine ≤ 1.5xULN)
Ethical/Other
Electrocardiography without clinical significant abnormalities
Written informed consent before inclusion according to the ICH-GCP and national/local regulations
Patients should use adequate birth control measures, during the study treatment period and for at least 3 months after the last study treatment
Women of childbearing potential need to have a negative pregnancy test 72 h before the application of the first dose of niclosamide
Patients who are breastfeeding must stop breastfeeding before the first dose of the study drug and not restart till 8 week after the last drug intake
**Exclusion criteria**
Concurrent conditions
Pregnant or lactating females
Other malignant disease (except colorectal cancer) within the last 5 years before inclusion in the trial except adequately treated basal cell carcinoma of the skin or squamous cell carcinoma of the skin, in situ carcinoma of the cervix. Patients with a malignant disease in history have to be free of disease for 5 years
Clinical significant heart disease like e.g. uncontrolled blood pressure; heart failure NYHA grade > 2; cardiac infarction within the last 12 months
Known uncontrolled concomitant disease despite treatment like e.g. chronic obstructive pulmonary disease
Known alcohol or drug abuse
Serious infection
Any psychological, familial, sociological or geographical condition, potentially hampering compliance with the study protocol and follow-up schedule
Ethical/Other
Participation in another interventional study within the last 30 days
Known hypersensitivity against a part of the study drug
Life expectancy < 3 months
Human immunodeficiency virus infection or active hepatitis B/C
Patients that are committed to an institution by official or judicial order
Persons that are depending on the sponsor, investigator or deputy

### Study intervention and general considerations for dose modifications

Patients will start the treatment with the oral intake of 2 g niclosamide on day 1 and will continue with the medication once daily at the same time after a meal till disease progression or toxicity. Toxicities will be graded according to NCI CTCAE v4.03.

In case of an allergic reaction or vomiting ≥ grade II or diarrhoea or nausea or any other toxicity ≥ grade 3 the study medication will be paused until recovery and consequently reduced by one dose level (500 mg). If dose reductions to levels less than 1 g or discontinuation of the study treatment longer than 3 weeks are necessary, the study treatment will be terminated.

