### Statistics

The study is a one-arm open-label clinical trial with interim analyses for futility of patients with metastatic CRC.

A Simon two-stage design will be used to allow early termination due to futility. The null hypothesis is that the probability of being free of progression (having stable disease, partial or complete response) at 4 months is p_0_ = 0.25 (H_0_: p < =p_0_ = 0.25) estimated according to the recent literature [50, 51]. This null hypothesis will be tested with the Binomial test one-sided against the alternative H_1_ (estimated progression-free probability at 4 months of the experimental therapy) p1 = 0.5. Samples size for both stages were calculated according to the optimal design after Simon [52].

In the first stage 17 patients will be recruited. If less than 5 of the first 17 patients are progression-free at 4 months the trial will be terminated prematurely. Otherwise 20 additional patients will be enrolled (up to a total of 37 patients).

The null hypothesis will be rejected if at least 13 patients out of 37 will be free of progression at 4 months. This design (optimal design after Simon) yields a type I error rate of 0.046 and a power of 0.902.

Analyses of PFS and OS survival will performed with Kaplan-Meier-curves, hazard ration will be reported with 95% confidence intervals. For safety analysis the worst toxicities in each cycle will be reported according to the National Cancer Institute (NCI) Common Terminology Criteria for Adverse Events (CTCAE) Version 4.03. A descriptive analysis of adverse events (AEs) and serious adverse events (SAEs) will be provided.

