### Assessments

Patients will be followed up closely for side effects. This includes physical examinations as well as blood tests. Additional intensive analyses of niclosamide levels in the blood will be conducted in the first patient cohort (patients 1–5) in the first week to examine the absorption of niclosamide from the intestine and systemic circulation. To assess efficacy imaging will be performed every 2 months to evaluate the disease status.

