## Discussion

Several research groups and our own studies could show that niclosamide inhibits crucial pathways associated with proliferation, migration and invasion like the Wnt/β-catenin pathway, leading to anti-cancer activity of the drug. Niclosamide is initially EMA- and FDA-approved for anti-helminthic treatment and has a good safety profile, which creates a solid basis for repositioning this drug for alternate uses. Our preclinical studies supported the strong potential of niclosamide as anti-cancer drug, which interferes with tumor progression and metastases formation via S100A4 inhibition. However, its application in cancer patients has not been investigated in patients yet. Therefore, the use of niclosamide represents a novel approach of particularly metastases intervention via inhibition of a defined molecular target, such as S100A4.

To better explore the therapeutic potential of niclosamide there is the need to conduct a clinical trial to investigate the safety, efficacy and pharmacokinetics of orally applied niclosamide in cancer patients, and most importantly, to investigate if niclosamide treatment will result in prolongation of the PFS of the patients. The attractiveness of this study is based on the fact that the drug activity in patients will be correlated with the molecular analysis of the target molecule S100A4 in patient’s blood as the easiest accessible liquid biopsy for the timely monitoring. Furthermore, potential limiting factors, such as possible intra-individual difference in the drug absorption rate, will provide important additional information to what extend this will lead to variations of its anti-cancer efficacy.

As there is currently no predictive biomarker for response to niclosamide available we included an intense translational research program in our study to gain deeper insights in the mechanisms of niclosamide mediated anti-cancer activity. Thus, exploring the therapeutic potential of niclosamide in colon cancer patients in correlation to its target molecule S100A4 will enable us to evaluate this approach for broader uses in cancer therapy, where Wnt-signaling interference represents a rationale.

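### The dose-modification rule has no upper grade for allergic reactions, so after a severe reaction that resolves within 3 weeks its default is re-exposure at 1.5 g; stopping is permitted but not required

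*Protocol article*

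**What the plan says.** All the dosing rules are in the protocol article, section *Study intervention and general considerations for dose modifications*.

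- **Dose.** Treatment starts at 2 g and is taken once daily "till disease progression or toxicity".
- **Trigger.** "In case of an allergic reaction or vomiting ≥ grade II or diarrhoea or nausea or any other toxicity ≥ grade 3".
- **Action.** "the study medication will be paused until recovery and consequently reduced by one dose level (500 mg" is the single action for all of these triggers.
- **Explicit termination.** Treatment ends under this condition: "If dose reductions to levels less than 1 g or discontinuation of the study treatment longer than 3 weeks are necessary".
- **Grading.** "Toxicities will be graded according to NCI CTCAE v4.03".

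Four other places bear on the point:

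- The exclusion criteria in Table 1 (*Recruitment process*) bar patients already known to be hypersensitive to a component of the study drug.
- The section on circulating S100A4 transcripts, under *Translational research*, schedules a blood sample when treatment ends and lists toxicity among the possible reasons for ending it.
- *Assessments* states: "Patients will be followed up closely for side effects".
- *Statistics* states: "For safety analysis the worst toxicities in each cycle will be reported".

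**The concern.** The trigger is more cautious for allergy than for most other toxicity. It applies from grade 2, or from any grade if the grade limit is read as belonging to vomiting alone, whereas other toxicity triggers at grade 3. The action is not more cautious. A severe allergic reaction is handled in the same way as grade 2 vomiting: wait for recovery, then continue 500 mg lower.

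At stake is the safety of a patient who has just shown a severe allergic reaction to niclosamide. The article offers nothing to support giving the drug again at a reduced dose in that situation. Its *Discussion* says of niclosamide that "its application in cancer patients has not been investigated in patients yet". The remarks on good tolerability in *Background* and *Discussion* are general and do not address re-exposure after an allergic reaction.

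**Working it through.** The article states no figure on this point that could be reproduced. The check is to follow the written rule for a patient with a severe allergic reaction.

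**Inputs** (all from the dose-modification section): starting dose 2.0 g; reduction step 0.5 g; termination if a dose below 1 g is needed, or if more than 3 weeks off drug is needed.

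**Step 1: does the trigger cover a severe reaction?** Yes, on either reading of the sentence. If the grade limit applies to allergy, grades 2 and above are covered. If it applies to vomiting only, all grades are covered. Neither reading takes severe reactions out of the rule.

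**Step 2: does an explicit termination condition apply?** Take a reaction that resolves within 3 weeks, with no earlier reduction for another toxicity. The time condition is not met. For the dose condition, the dose after reaction *k* is 2.0 − 0.5 × *k* g:

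| Reaction | Next dose | Below 1 g? | Default under the rule | Share of starting dose |
|---|---|---|---|---|
| 1 | 2.0 − 0.5 = 1.5 g | no | restart | 1.5 / 2.0 = 75% |
| 2 | 1.5 − 0.5 = 1.0 g | no (equal to 1 g) | restart | 1.0 / 2.0 = 50% |
| 3 | 1.0 − 0.5 = 0.5 g | yes | terminate | – |

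The default therefore allows up to two re-exposures. The dose condition itself first forces a stop at the third reaction.

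**Step 3: are the restart doses small?** No. *Background* gives the adult anti-helminthic regimen as 2 g on the first day and 1 g daily for the next 6 days. The restart doses of 1.5 g and 1.0 g are above or equal to that 1 g daily dose.

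**Step 4: does any other text require a stop?** The general phrase on treatment duration and the sampling text under *Translational research* both recognise toxicity as a reason to end treatment. Neither names a type or grade of toxicity at which treatment must end. *Assessments* provides for monitoring and *Statistics* for reporting. Neither directs an action.

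**Step 5: comparison with eligibility.** A patient with a severe allergic reaction attributed to niclosamide has acquired a condition that Table 1 would have treated as a bar to entry. The dose rule nevertheless has continued dosing as its default.

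**With the added stop at grade 3 or higher:** default re-exposures after such a reaction fall from up to 2 to 0. Handling of lower grades is unchanged.

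**The case against.** **The article condenses a fuller protocol.** Detailed discontinuation criteria are often left to that document, which may contain a hypersensitivity stop. This is a fair limit on confidence, and the absence of such a stop from the full protocol cannot be asserted. But the article is not merely silent. It names allergic reactions and assigns them an action, and that published rule is what the point addresses.

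**The investigator can stop.** This stands. A reader might infer that the plan obliges re-exposure, or that an investigator who stops after a first severe reaction breaks the protocol. The documents do not support that. Both the treatment-duration phrase and the sampling text allow treatment to end for toxicity, and a longer interruption can be judged necessary. What remains is that the stop is discretionary, while the specific rule points the other way.

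**Three reactions are improbable.** A reader might take the table above to mean that three severe reactions have to occur before anyone stops. That needs each reaction to resolve within 3 weeks, no reduction for another cause, and an investigator who twice declines to stop. The count describes where the dose condition first bites and is not a forecast. The point already holds at the first restart.

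**Restart is only implied.** This is correct: the text says the drug is paused and then reduced. A reduced dose is still a dose taken, so resumption is the natural meaning.

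**The drug is reported as well tolerated, and known hypersensitivity is excluded at entry.** Both bear on how often the situation would arise. Neither says what to do when it does.

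**Conclusion.** The point holds as a gap in a stated safety rule. For a severe allergic reaction that resolves within 3 weeks, the default written action is re-exposure at 1.5 g, and at 1.0 g after a second reaction. Ending treatment is allowed but not required. This sits badly with the exclusion of patients with known hypersensitivity.

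The count of up to two default re-exposures rests on three assumptions: a start at 2 g, no reduction already used for another toxicity, and recovery within 3 weeks each time. The article gives no rate of allergic reactions, so neither a probability of occurrence nor an expected harm can be derived.

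A reader might look for a consequence for the trial's statistics. There is none: sample size, error rates and the primary analysis are unaffected. It is a cheap improvement in patient safety. Confidence is medium, because the full protocol is not shown.

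**What to change.** Add one sentence to the dose-modification section:

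*Niclosamide is permanently discontinued after any allergic reaction of CTCAE v4.03 grade 3 or higher attributed to the study drug.*

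Keep pause-and-reduce for lower-grade allergic reactions. The section already uses both the grading scale and the grade 3 cut-off, so no new definition is needed. A further stop after a second grade 2 reaction would be optional. The article gives no basis for it, and the point does not depend on it.

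The cost is one sentence in a protocol amendment, with no change to the design or the analysis. The downside is that a few patients may stop niclosamide earlier than under the present text. If the full protocol already contains such a stop, no change to trial conduct is needed and only the published summary of the rule is incomplete.

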### Assessments

Patients will be followed up closely for side effects. This includes physical examinations as well as blood tests. Additional intensive analyses of niclosamide levels in the blood will be conducted in the first patient cohort (patients 1–5) in the first week to examine the absorption of niclosamide from the intestine and systemic circulation. To assess efficacy imaging will be performed every 2 months to evaluate the disease status.

### Translational research

Patients will be asked to consent for optional translational research including analysis of patients’ tumor tissue and additional blood analysis as described hereunder.

#### Analysis of S100A4 expression in patient primary tumors and/or metastases or recurrent tumors

If available, tumor tissue of the primary tumor and/or metastasis or recurrent tumor will be collected for patients who consent for optional translational research to do further analyses in specific subgroups (responder/non-responder). These tissues will be analyzed for S100A4 expression. These initial analyses characterizing the molecular starting point of the patient, depend on the availability of the amount of tissue procured for research purposes.

#### Analysis of potential niclosamide-induced effects on circulating S100A4 transcripts in patient plasma

The following initial analyses for characterization of the molecular starting point of the patient will be performed by using patients’ plasma for determination of the basal levels of circulating S100A4 transcripts.

Peripheral blood samples will be collected at baseline and at end of treatment (due to progression, toxicity or other reasons) for all patients. For patients who consented for the optional translational research additional blood samples will be collected during routine blood taking at week 1, week 4 and thereafter monthly until progression. Blood samples will be used to discover and validate the prognostic and predictive value of S100A4 as well as for response to niclosamide and to evaluate relationship between other clinical outcome parameters.

#### Plasma generation

Immediately after every blood taking, plasma will be generated. Blood initially collected in EDTA tubes will be processed in the lab for generation of plasma aliquots (400 μl volume) which will be stored frozen at − 80 °C. Analysis will be performed after completion of collection of all samples.

Additional analyses of further circulating transcripts such as beta-catenin might follow in patients who consented for the optional translational research.

#### Determination of niclosamide plasma concentration

Plasma samples (400 μl) are supplemented with acetonitrile (800 μl) containing naproxen (0.25 μg/ml). The mixture is vortexed for 30 s and centrifuged at 15000 g for 20 min at room temperature. An aliqoute of 800 μl of supernatant is withdrawn and evaporated to dryness (N2, 50 °C). The samples were reconstituted in 400 μl dilution solvent consisting of acetonitrile/methanol/water (5%/5%/90%, *v*/v/v) and subjected to HPLC.

HPLC (Shimadzu) will be performed with Trentec Select columns (RP C8 120 ODS3 5 μm; 125 × 3,0 mm with guard column; mobile phase A: acetonitrile/water/phosphoric acid (70/30/0.1, *v*/v/v); mobile phase B: acetonitrile/water/phosphoric acid (25/75/0.1, v/v/v); gradient: 0.01 min B 70%; 8 min B 70%; 8.1 min B 0%; 25 min B 0%; 25.1 min B 70%; flow rate: 0.5 ml/min). Time of analysis is 50 min, injector volume is 100 μl, detection l ABS [nm] is performed at 250 nm.

HPLC calibration curves of naproxen and niclosamide are linear in the range of 0.05 to 1 μg/ml concentration of each analyte of a dilution series in dilution solvent (= acetonitrile/methanol/water (5%/5%/90%, v/v/v). The parameters of a linear regression equation are as follows, naproxen: R2 = 0.9999, y = 216,017×; niclosamide: R2 = 0.9937, y = 230,993× confirming a good linearity for both analytes.

Determination of niclosamide in human plasma samples is done by HPLC (BioTez GmbH, Berlin).

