Niclosamide has only little side effects and seems to be well tolerated even when applied over a long period [49]. The oral dose of niclosamide for adults in anti-helminthic treatments is 2 g on day one followed by 1 g daily for 6 consecutive days. The serum concentration of niclosamide after a single dose of 2 g leads to maximal serum concentrations of 0.25–6.0 μg/ml which corresponds to the concentration used on the above mentioned models [34, 49].

As there is strong evidence from in vitro and in vivo experiments that niclosamide might be beneficial as anti-tumorigenic and anti-metastatic drug we designed the hereafter described clinical trial to investigate the safety and efficacy of orally applied niclosamide in patients with metachronous or sychronous metastases of a CRC who progressed after therapy and for whom no other standard therapy is available.

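### Niclosamide is calibrated in solvent that skips the plasma work-up, and linearity rests on R2 alone, so neither the accuracy of absolute plasma levels nor low-end accuracy is established

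*Protocol article*

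**What the plan says.** All assay details are in the protocol article, section Determination of niclosamide plasma concentration.

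- **Patient samples.** "Plasma samples (400 μl) are supplemented with acetonitrile (800 μl) containing naproxen (0.25 μg/ml"). After centrifugation, "An aliqoute of 800 μl of supernatant is withdrawn and evaporated to dryness" at 50 °C. The residue is taken up in 400 μl of a solvent that is 90% water and injected.
- **Calibrators.** The standards span 0.05 to 1 μg/ml and are made up as "of each analyte of a dilution series in dilution solvent". They undergo none of the steps above.
- **Evidence of quality.** One line per substance: "naproxen: R2 = 0.9999, y = 216,017" times concentration, and "niclosamide: R2 = 0.9937, y = 230,993× confirming a good linearity for both analytes". No intercept, weighting, number of levels or back-calculated accuracy is given.
- **Role of naproxen.** It is present from the precipitation step onward and has its own line. The section does not call it an internal standard, does not say that niclosamide results are corrected by it, and gives no peak-ratio line.

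Study objectives plans a pharmacokinetic analysis of plasma concentration and its possible correlation with efficacy. Assessments adds intensive sampling in patients 1–5 to examine absorption. Background supplies an absolute reference: a single 2 g dose "leads to maximal serum concentrations of 0.25–6.0 μg/ml which corresponds to the concentration used on the above mentioned models".

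**The concern.** Standards in solvent measure detector response only. Niclosamide lost to the protein pellet, on drying or on redissolving lowers the patient signal but not the standards, so it is read as a lower plasma concentration. A substance added before extraction removes this error only if it is used in the calculation and is lost to the same degree. Naproxen arrives with the precipitant, whereas niclosamide is already in the plasma, so equal recovery has to be shown.

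The second issue is the inference from R2. Over a 20-fold range (0.05 to 1 μg/ml) R2 is dominated by the upper standards and says little about relative error at the bottom. An absorption question depends most on the low values.

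At stake are the absolute concentrations reported, their comparison with the range in Background, and the precision of values from poor absorbers.

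**Working it through.** The stated R2 cannot be reproduced, because no calibration data are given. What can be checked is what the described method implies.

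**1. Volume balance** (inputs: 400 μl plasma, 800 μl acetonitrile, 800 μl supernatant taken, 400 μl for reconstitution, naproxen 0.25 μg/ml in the acetonitrile).

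- Vial/plasma ratio at full recovery: 400/1200 × 800/400 = 0.667.
- Naproxen in the vial: 0.25 × 800/1200 × 800/400 = 0.333 μg/ml, inside its calibration range.
- A plasma level of 0.25 μg/ml is read at 0.25 × 0.667 = 0.167 μg/ml.
- The lowest standard, 0.05, corresponds to 0.05/0.667 = 0.075 μg/ml in plasma.

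**2. Bias in the absolute concentration.** Recoveries are not stated. Assume 60–100% for each substance.

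- Without naproxen correction, bias = recovery − 1: −10% at 90% recovery, −30% at 70%, −40% at 60%.
- With naproxen correction, bias = (niclosamide recovery / naproxen recovery) − 1.

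| Niclosamide recovery | Naproxen recovery | Bias |
|---|---|---|
| 60% | 100% | −40% |
| 80% | 100% | −20% |
| 80% | 80% | 0% |
| 100% | 80% | +25% |
| 100% | 60% | +67% |

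The error can go in either direction and vanishes when the recoveries match.

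**3. What R2 = 0.9937 implies if error is constant over the range.** For a line through the origin, s = √(SSE/(n−1)) in concentration units, with SSE = (1 − R2) × Sxx. The levels are not stated, so four plausible sets of 5 to 11 levels were tried.

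- Example {0.05, 0.1, 0.25, 0.5, 1}: Sxx = 0.603, SSE = 0.0063 × 0.603 = 0.0038, s = √(0.0038/4) = 0.0308 μg/ml.
- Over the four sets: s = 0.026 to 0.031 μg/ml.
- Relative to the 0.05 standard: 51–62%.
- Relative to 0.167 in the vial (0.25 in plasma): 0.026/0.167 = 15% to 0.031/0.167 = 19%.
- If the software reported the uncentred R2 often used for lines through the origin, s would be 0.046 to 0.049 μg/ml, or 92–99% of the 0.05 standard.

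**4. What the same R2 implies if error is proportional.** Simulated lines with constant CV (4,000 per setting) had a median R2 near 0.9937 at a CV of about 5% (11 levels), about 8% (6 levels) and about 11% (5 levels). That error would be acceptable at every level, including 0.05.

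R2 cannot distinguish case 3 from case 4.

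**The case against.** **Naproxen is there to control recovery.** It passes through the whole work-up and has its own calibration line, and correcting for loss is the natural reason to add it at that step. A reader might infer that extraction loss goes uncorrected; the article does not support that. What stands is narrower: use of the correction is not stated, the results shown are two separate external lines, and matching recovery is not shown.

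**Poor low-end accuracy is not demonstrated.** A reader might take the 51–62% figure as the assay's actual error. It holds only under constant error, and proportional error fits the same R2. Nor does the article say that the fit is unweighted. The objection is right that inaccuracy is unproven, but the article's own conclusion from R2, "confirming a good linearity for both analytes", gives no assurance about the low end either.

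**No patient is classified against 0.25 μg/ml.** The range in Background is context, and no analysis uses it as a cut-off, so a claim that patients would be mislabelled is not supported. A recovery factor that is the same in all samples also leaves patient ranking, and hence a rank correlation with efficacy, unchanged. This stands. The absolute levels remain exposed, as does any loss that varies between samples if naproxen is not used.

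**A journal article condenses.** A separate laboratory is named for the plasma determinations, and a validation report with plasma recovery and quality controls may exist. Their absence here is therefore not the finding. The point concerns what the article does fix: the calibrator matrix, separate lines per substance, and R2 as the support for linearity.

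**Conclusion.** The point holds in limited form. As described, the calibration does not establish the accuracy of absolute plasma concentrations, because it bypasses the work-up and depends on a match in recovery that is not shown. With naproxen correction the bias runs from −40% to +67% if each recovery lies between 60% and 100%; that range is an assumption, and zero lies within it. R2 = 0.9937 leaves low-end accuracy open: roughly 15–19% relative error at a plasma level of 0.25 μg/ml under constant error and centred R2, or about 5–11% under proportional error. Both rest on assumed calibrator levels.

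The documents do not show that reported values are biased, that low values are inaccurate, or that any patient would be misclassified. The effect is confined to the pharmacokinetic analysis and its exploratory correlation with efficacy. Progression-free status at 4 months, the two-stage rule and safety do not depend on it. Minor, but worth changing because it is cheap.

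**What to change.** 1. State how naproxen enters the calculation, and quantify niclosamide by the niclosamide/naproxen peak ratio instead of two separate lines.
2. Prepare calibrators and quality controls in blank human EDTA plasma and take them through the identical work-up in every run. A proportional loss common to calibrators and samples then cancels, without assuming equal recovery of the two substances.
3. Fit by weighted regression (1/x or 1/x²), with the weight chosen from the observed spread at each level.
4. Set the lower limit of quantification at the lowest level with acceptable back-calculated accuracy and precision (for example within 20%), and report values under it as below quantification.
5. Replace R2 as the evidence of linearity with back-calculated accuracy at each level. If plasma validation data already exist, cite them.

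Cost: blank plasma, a few extra vials per run and a revised assay description, with no patient burden. The lower limit may turn out less favourable than 0.05 μg/ml in the vial (0.075 μg/ml in plasma).
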